## 6. Conclusions

The results of this trial will provide an in-depth understanding of the efficacy of early interlimb-coordinated intervention on gait and upper functional rehabilitation and how it may relate to the neural plasticity process.

## Figures and Tables

**Figure 1 brainsci-11-01495-f001:**
[figure not shown]
Flow diagram of the study procedure.

**Figure 2 brainsci-11-01495-f002:**
[figure not shown]
Event related potential paradigm to measure contingent negative variation.

**Figure 3 brainsci-11-01495-f003:**
[figure not shown]
Bicycle ergometer for interlimb coordinated intervention.

**Table 1 brainsci-11-01495-t001:** A brief description of each of the secondary outcome measure that will be recorded at all participating centres.

Fugl-Meyer Assessment of Motor Recovery (FMA) [46]	It is a validated tool to evaluate motor function, balance, and joint function in stroke-related hemiplegic patients. The interpretation of FMA is as follows: <50 = Severe; 50–84 = Marked, 85–94 = Moderate; 95–99 = Slight.
Berg Balance scale (BBS) [47]	The BBS consists of 14 balance-related tasks that include sit to stand, stand to sit, and standing on one foot. It was developed to assess the ability to maintain dynamic and static balance.
Timed up and go test (TUG)	The test requires the person to rise from a chair and walk 3 m at a comfortable pace, turn around at the 3 m mark, and walk back to the starting point. The test’s score is the time it takes the person to complete the test. A cut off of 14 s was proposed to be “normal” [48].
Action Research Arm Test (ARAT) [49]	ARAT is a 19-item test that is divided into four sub-tests, which consist of grasp, grip, pinch, and gross arm movement. A score of between 0 to 4 is given to each task: 0—can perform none of the test; 1—performs part of the test; 2—takes abnormally long or has great difficulty in completing the test; 3—able to perform the test normally.
Instrumental Activities of Daily Living (IADL) [50]	The IADL [26] is a functional disability scale that assesses the functional level by asking whether a person receives personal help with daily living activities, such as using the telephone, getting to places outside the house, grocery shopping, preparing meals, doing housework or handyman work, laundry, taking medications, and managing finances.
Electroencephalography (EEG)/Event related potential (ERP)	Parameters of contingent negative variation (CNV), alpha, beta, gamma, and theta wave oscillation.
Functional magnetic resonance imaging (fMRI)	The voxel count T1-weighted data set of the entire brain will be acquired for each participant. The scan parameters for blood oxygen level-dependent weighted scans are as follows: TR = 200 ms, TE = 25 ms, field of view 200 × 200, matrix 64 × 64, and a slice thickness of 3 mm.
Functional Near-Infared Spectroscopy (fNIRS)	The optical system used in the study will be a multi-channel frequency domain NIRS system (BRITE, Artinis Medical Systems, Gelderland, The Netherlands). The particular regions of interest is motor cortex (M1), supplementary motor cortex (SMC), and premotor cortex (PMC).

**Table 2 brainsci-11-01495-t002:** SPIRIT diagram for the study.

	Enrolment	Allocation	Post-Allocation			
Timepoint	0	0	Baseline	3 Weeks Intervention	3 Months	6 Months

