## 2. Materials and Methods 

### 2.1. Study Design

This study is a parallel, single-blinded, multi-center randomized controlled trial to evaluate the effect of interlimb-coordinated intervention on gait and motor function recovery in patients with acute stroke. 

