### 2.5. Randomization

Eligible participants will be randomly assigned to either the experimental or the control group at a ratio of 1:1 without stratification. A statistical expert from the Faculty of Medical Statistics and Epidemiology, Sun Yat-sen University, computed the random allocation sequence. The sequence will be uploaded onto a central operating system. Research team members will access the system at the time of participant enrolment by dialing the central phone number to obtain the allocation. The operating system will provide the numbers of 001 and 002, which correspond to the intervention group and control group, respectively. Each participant will be assigned a unique identification number to maintain confidentiality. 

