### 2.7. Outcome Measures

#### 2.7.1. Primary Outcome Measure

The primary outcome measure is gait speed, which will be assessed by the 10 m walk test. 

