### 2.11. Outcome Assessments

Each centre has a dedicated multidisciplinary assessment team who are specifically trained to deliver the outcome assessments. Team members consist of occupational therapists, physiotherapists, physicians, and nurses who will be blinded to the group allocation. 

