### 3.2. Intervention Group

The intervention group will receive interlimb-coordinated training for 20 min in addition to conventional training. Each of the conventional rehabilitation components will be shortened to reduce the overall conventional therapy program duration for a total of 20 min in the intervention group. This is to give equivalent therapeutic time among the two groups. Interlimb-coordinated training will be conducted on a bespoke bi-cycle ergometer where participants will be asked to perform arm and leg cycling simultaneously. A diagram of the bespoke bi-cycle ergometer is illustrated in Figure 3. The 20 min of interlimb-coordinated training will be divided into 10 min of active cycling and 10 min of active-assisted cycling. In active-assisted mode, the participants will be asked to primarily lead the movement with the paretic side, and assistance will be provided by the ergometer’s motor, which reduces the effort required from the participant. The bespoke bi-cycle ergometer is designed to have a separate motor on the left and right sides to ensure that assistance is only provided to the paretic side. In active cycling mode, the four motors that power the handlebars and pedals are linked to enable a synchronized reciprocal cycling motion of the upper and lower limbs simultaneously. Participants will be asked to cycle at a work rate that would provide a score of between 10–13 (light–somewhat hard) on the Borg’s Rating of Perceived Exertion scale [56]. The exact work rate on the cycle ergometer could not be pre-determined or fixed for every participant, as each participant is likely to have a different exercise capacity. Thus, a subjective Borg scale was adopted as an index to monitor work rate intensity. 

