### 4.2. Data Analysis

All statistical analyses will be performed in IBM SPSS version 21 software (SPSS Inc., Chicago, IL, USA). Descriptive statistics will be conducted to describe the sample population. The demographic characteristics and baseline results for the primary and secondary outcome measures will be analyzed using analysis of variance (ANOVA) or Chi-square test for categorical data. A mixed-effect model analysis will be adopted to compare changes in all of the outcome measures between groups at the completion of the intervention and at the 3- and 6-month follow-ups. The mixed-effect model analysis will include treatment, time, and centre as fixed effects, and the participants will be included as the random effect. Changes in the outcome measures will be adjusted for age, sex, centre, and time. The level of statistical significance will be set at *p* < 0.05. Cohen’s d will be calculated to measure the effect size of the difference for every comparison. The effect size will be interpreted as follows: 0.2—small effect size; 0.5—medium effect size; and 0.8—large effect size. Stratification analysis will be conducted to explore the potential effect difference between centres. There are no planned interim analyses or stopping rules, as the power calculation has accounted for loss to follow-up. In the event of missing data during the follow-up period, the modified intention to treat principle will be followed with the last observation carried forward method. 

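### As scheduled, the baseline tests follow allocation, so an unmasked participant's baseline performance could depend on the arm assigned

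*Protocol article*

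**What the plan says.** **Schedule.** Table 2 runs through three blocks: Enrolment, Allocation and "Post-Allocation". Baseline is the first column of the third block. Gait speed, EEG, fNIRS, MRI, BBS, ARAT, FMA-UL and IADL all have their first mark there. The first two blocks hold only screening, consent and the allocation itself.

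**Allocation.** Section 2.5: "Research team members will access the system at the time of participant enrolment by dialing the central phone number to obtain the allocation".

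**Blinding.** Section 2.1: "This study is a parallel, single-blinded, multi-center randomized controlled trial". Section 2.11 identifies the blinded party as the assessment team, "who will be blinded to the group allocation". Section 3.2 describes the experimental treatment: "Interlimb-coordinated training will be conducted on a bespoke bi-cycle ergometer where participants will be asked to perform arm and leg cycling simultaneously".

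**Outcome and analysis.** Section 2.7.1: "The primary outcome measure is gait speed, which will be assessed by the 10 m walk test". Section 4.2: "A mixed-effect model analysis will be adopted to compare changes in all of the outcome measures between groups". The model terms listed there are treatment, time and centre, with adjustment for age, sex, centre and time. The baseline value of the outcome is not listed.

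**The concern.** A baseline measured before allocation cannot depend on the arm, and that is what makes it a sound reference for change. A baseline measured after allocation loses this protection once the participant knows the arm. The 10 m walk, BBS, ARAT and FMA all depend on how hard the participant tries. Someone pleased or disappointed by the allocation may perform differently on the first test. A blinded assessor can time and score that performance fairly and still record a value that the arm has influenced.

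At stake is the reference point for the primary comparison and for the other effort-dependent outcomes. Higher effort at baseline in one arm makes that arm's gain look smaller, and lower effort makes it look larger. The distortion could favour either arm.

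**Working it through.** **1. Order of events.** Table 2 places allocation before baseline. Section 2.5 fits that order, because the call is made at enrolment. Sections 2.3 (recruitment and consent) and 2.7.2 (assessment times) do not place baseline testing before the call. Nothing in the text says that the arm is withheld from the participant until testing is done.

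**2. Who may know the arm at baseline.** The team member who makes the call knows it. The assessors should not. The participant may: the trial is single-blinded, the assessors are the blinded party, and ergometer training cannot be disguised as conventional therapy. This step is an inference; no sentence says when the participant is told.

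**3. How a shift enters the estimate.** Let Δ be the true treatment difference. Let s be the arm-related shift (intervention minus control) in mean performance at baseline, and t the same quantity at a follow-up visit.

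- Difference in change from baseline: Δ + t − s. The same holds if baseline enters the mixed model as one of the time levels, since the contrast is still a difference in change.
- Baseline as a covariate, with equal SDs and baseline–follow-up correlation ρ: Δ + t − ρs.
- Baseline taken before allocation: s = 0 in expectation, leaving Δ + t under either analysis.

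The baseline shift therefore passes in full into a change contrast. Baseline adjustment would reduce it but not remove it. Reordering removes s and leaves t, which belongs to any trial with unmasked participants.

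**4. Scale, under assumed shifts.** The document gives no value for s. The values below are arbitrary and serve only to show scale. From section 2.12 come SD = 0.75, n = 103 per arm, the planned difference of 0.3 m/s and the minimal clinically significant difference of 0.16 m/s. That section's total of 206 reproduces: with f = 0.2 and assumed m = 4 visits and ρ = 0.5, λ = f²Nm/(1 + (m − 1)ρ) = 0.04 × 206 × 4/2.5 = 13.18, which gives power 0.951.

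Set Δ = 0 and t = 0, and take one follow-up visit with a two-sided 5% test.

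- Change score: SE = 0.75 × √(2(1 − ρ)) × √(2/103). For ρ = 0.5 this is 0.1045. Bias is s in size.
- Baseline-adjusted: SE = 0.75 × √(1 − ρ²) × √(2/103). Bias is ρs in size.
- Type I error = 1 − Φ(1.96 − bias/SE) + Φ(−1.96 − bias/SE).

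| Assumed s (m/s) | s/0.3 | s/0.16 | Change score, ρ = 0.5 | Change score, ρ = 0.7 | Adjusted, ρ = 0.5 | Adjusted, ρ = 0.7 |
|---|---|---|---|---|---|---|
| 0.03 | 10% | 19% | 0.060 | 0.066 | 0.053 | 0.059 |
| 0.05 | 17% | 31% | 0.077 | 0.095 | 0.059 | 0.076 |
| 0.10 | 33% | 63% | 0.160 | 0.235 | 0.086 | 0.155 |

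Small shifts do little harm and larger ones matter. The document does not say which case applies.

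**The case against.** The strongest reply is that the exposure is inferred. Section 2.5 says that the team obtains a code; it does not say that the participant hears it before testing. Table 2 is also loosely drawn elsewhere: it labels the intervention as three weeks where the text has two, leaves the intervention rows blank and omits the TUG listed in Table 1. A misplaced heading is plausible. Figure 1, not available here, may show another order. All this stands, and it limits the point to what the schedule permits. It does not remove the point, because the only order given in the text is allocation first and section 2.5 is consistent with it.

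Four stronger readings are tempting, and the document does not support them.

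- **Every change score is biased by the baseline shift.** Follow-up tests are also done by participants who know their arm, so the net bias is t − s, and a lasting effort effect would partly cancel. IADL asks about help received and is not an effort test.
- **The shift is about 0.03 m/s.** That figure appears in the Introduction as a gain from traditional gait therapy. Nothing links it to an effect of knowing one's allocation, so 19% of 0.16 m/s is not an estimate of the bias.
- **Participants who leave between allocation and baseline drop out of the analysis.** Section 4.2 invokes modified intention to treat with last observation carried forward for missing follow-up data. It does not say how a missing baseline is handled.
- **Reordering is free because both steps fall on the same day.** The document does not say that they do.

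**Conclusion.** The point holds as a weakness in the stated order of events, and it should be corrected. Followed as written, the plan takes its baseline after the arm is assigned, in participants who cannot be masked to treatment, and then compares changes from that baseline without listing it as an adjuster. An arm-related shift at baseline would enter the change contrast, and assessor blinding would not prevent this.

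Whether any shift would occur, how large it would be and which arm it would favour cannot be derived from the document. The conclusion assumes that Table 2 shows the intended order and that participants may learn their arm before testing. If the arm is withheld until testing is complete, the risk largely goes, but the plan should say so. The sample size is not affected.

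**What to change.** State in section 2.5 that at least the clinical performance baseline tests (10 m walk, BBS, TUG, ARAT, FMA), and preferably all baseline assessments, are completed and recorded after consent and before the allocation call. Move the Baseline column ahead of Allocation in Table 2, and check that Figure 1 shows the same order. If the table is only mislabelled, the same edit corrects it.

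The change adds no assessment and leaves the sample size as it is. Its cost is that allocation waits until the baseline tests are done. If MRI, EEG and fNIRS are included, that may mean a short delay; requiring only the clinical tests first would limit it and still protect the primary outcome.

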**Enrolment:**						
Eligibility screen	X					
Informed consent	X					
**Allocation**		X				
**Interventions:**						
Routine with Interlimb coordinated						
Routine rehabilitation						
**Assessments:**						
Gait speed			X	X	X	X
EEG			X	X	X	X
fNIRS			X	X	X	X
MRI			X	X	X	X
BBS			X	X	X	X
ARAT			X	X	X	X
FMA-UL			X	X	X	X
IADL			X	X	X	X

**Table 3 brainsci-11-01495-t003:** Time allocation for each treatment in the control and intervention groups.

	Time (Minutes)	
Treatment Type	Control	Intervention
Muscle strengthening	20	17
Treadmill gait training	20	17
Balance training	20	17
Passive exercise	10	7
Upper limb training	20	17
Functional practice	20	17
Neuromuscular electrical stimulation	10	8
Interlimb coordinated	0	20
Total	120	120

## Data Availability

Not applicable.
